#### **3.2. End-of-study KAP survey of female and male clients**

In the final three months of the study, a convenience sample of approximately 28 female clients and 28 male clients will be recruited from each of 18 sites (N=488 female and 488

male patients). All 976 participants will complete the family planning KAP survey that was used at baseline with additional questions about the acceptability of family planning services offered at the site. Note that some of these participants may have also participated in the baseline KAP survey. The final version of the survey will be submitted to the IRB prior to initiating data collection.

The survey will be administered face-to-face by an interviewer in the respondent's preferred language in a private area of the centre. Inclusion criteria for the client KAP survey will be: 1) HIV-positive woman or man obtaining care at the FACES site, 2) not currently pregnant (if female), 3) age 18 to 45 years old if female and age 18+ if male; and 4) willing and able to give informed consent. Participants will be excluded if they do not meet the inclusion criteria listed above. Participants will be reimbursed a maximum of USD\$3 (approximately 200 Kenyan Shillings at current exchange rate) for transport.

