## **STUDY DESIGN/METHODOLOGY**

### **Overview**

The study will have three parts. During the first part (3 months), baseline data on contraceptive prevalence and unintended pregnancy will be collected at 18 PSCs that are supported by the FACES program in Suba, Kisumu East, Rongo and Migori Districts. Also during this first part, information about knowledge, attitudes and practices related to family planning will be obtained from patients and from clinicians at the sites. During the second part (3 months), an intervention consisting of integrating family planning services will be designed and implemented at twelve of the 18 FACES-supported PSCs. We aim to utilize a 2:1 integration:control model, with delayed integration so as to gradually expand the integration of FP and HIV services throughout the 18 sites, while maintaining the ability to test hypotheses on the effects of integration on health outcomes. After collecting the baseline data, we plan to stratify the clinics into two categories based on the overall patient volume and differences in the structure of family planning provision, i.e., whether or not there is a specific MCH division providing family planning at the site or not. Randomization of sites will then occur among clinics in each of these strata, with a ratio of two intervention sites (integrated model) to one control site (family planning provided in the standard manner at the site). During the third and last part (9 months), data on contraceptive prevalence and unintended pregnancy will be collected from each of the 18 sites. At the end of part three, information about knowledge, attitudes and practices related to family planning again will be obtained from female patients and from clinicians at the sites. In addition, we will administer questionnaires assessing the acceptability of family planning services to patients, and in addition clinic staff will be answer a questionnaire assessing the feasibility of providing integrated family planning services.

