### **1.2. Baseline knowledge, attitudes and practices (KAP) survey of female and male clients**

Also during this three-month period, a convenience sample of approximately 28 female patients and 28 male patients will be recruited from each of the 18 sites (N=488 female and 488 male patients) to complete a questionnaire regarding knowledge, attitudes and practices (KAP) related to family planning. The purpose of the KAP survey is both to 1) measure the satisfaction with the family planning services offered at the HIV care and treatment clinic, 2) provide information that will be used to design the family planning integration intervention and improve family planning provision, and 3) provide a baseline measure of KAP that will be compared to follow-up surveys at the end of the study.

The survey will be administered face-to-face by an interviewer in the respondent's preferred language in a private area of the centre.

The inclusion criteria for the client KAP survey will be:

- 1) HIV-positive woman or man obtaining care at the FACES site
- 2) Not currently pregnant (if female)
- 3) Age 18 to 45 years old if female; age 18+ if male
- 4) Willing and able to give informed consent

Clients will be excluded if they do not meet the inclusion criteria listed above. Some of the topics included in the KAP survey will be: familiarity with contraceptive methods; prior and current contraceptive use; partner's role in contraceptive decision-making; interest in preventing pregnancy in the future; and acceptability of and satisfaction with currently-offered family planning services at the site. The survey will be adapted from the Demographic and Health Survey modules on contraception, marriage and sexuality, and fertility preferences (see Appendix B1-1 for women's survey and Appendix B1-2 for men's survey). We will train our interviewers to provide referrals for women who need counseling or support services to a local women's non-governmental organization (NGO) working in Migori District, the Women's Action Forum for Networking (WAFNET). These referrals will be provided to women who report domestic abuse (psychological, physical, or sexual) or other negative events during the interviews. Participants will be reimbursed a maximum of USD\$3 (approximately 200 Kenyan Shillings at current exchange rate) for transport.

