## 2.2 Intervention implementation

After the intervention is fully designed, it will be implemented at twelve “intervention” FACES-supported PSC’s using a model that will ultimately include integrating HIV and FP services in all 18 sites. Implementing the intervention will consist of:

- Training clinic staff in family planning counseling and method provision
- Introducing family planning assessments into all clinic visits via incorporating inquiries as to family planning needs on all medical forms, thereby prompting provider questioning
- Introducing new client counseling sessions and education materials into the PSC care infrastructure
- Devising a system of procuring, inventorying and dispensing contraceptive methods, including at the very least condoms, oral contraceptives and injectables. At sites where it is feasible, IUDs and implants will also be made available. When a method is not available at the site (such as in the case of surgical sterilization), clients will be referred to nearby centers that offer the method.

At both the intervention and control sites, a brief family planning module will be integrated into the standardized clinic encounter form that is used at each client visit. This module will prompt the clinician to ask if the client is currently using contraception and his or her fertility intentions. Simply put, if the client is using a method, the provider will be ask if he or she is interested in changing the method; if the client is not using a method and does not desire pregnancy, the provider will be ask if he or she is interested in starting a method.

- At “intervention” sites clients will then be extensively counseled about contraception and will be provided any needed contraceptive methods on site.
- At “control” sites, clients will be provided with contraceptive services through the centers’ standard mechanisms, which generally involve referral to an affiliated family planning program that may or may not be on-site.

Prior to implementation of our intervention, we will resubmit the protocol for review at SSC/ERC for review of the final design of any educational materials developed.

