### **Study and data management**

The proposed study will utilize administrative offices at Suba District Hospital and/or Migori District Hospital. The study will maintain space for a desk, computer, and a locking file cabinet. The 18 study sites will be clinics within Suba, Kisumu East, Rongo and Migori District MOH. The study staff will include a study coordinator and a team of local language interviewers/research assistants. The study coordinator, under investigator guidance, will supervise the data collection, assist in intervention design, oversee the intervention implementation, and conduct regular site visits. He or she will also be responsible for data checking, quality control, and overall management of the data. Local language interviewers /research assistants will be responsible for abstraction of data from patient records and for conducting all interviews with clients and providers.

Digital recordings of the open-ended interviews with clients and clinic staff will be uploaded to a computer and transcribed into MS Word files by staff experienced in transcription, who will not have access to any identifying information on the participants. Recording and transcription files will be password-protected. Data from the surveys performed with female clients and clinic staff will be entered into SPSS by a member of the research team. These files will also be password-protected.

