### **ENDPOINTS**

**Primary Outcomes** (data abstracted from clinic encounter forms from all HIV-positive clients):

1. Contraceptive prevalence
  - a. Will compare post-intervention data from intervention sites to data collected over same time period from control sites
2. Pregnancy rate (number of pregnancies/number of unique clients seen during post-intervention data collection period) and percent of pregnancies that are unplanned
  - a. Will compare post-intervention data from intervention sites to data collected over same time period from control sites

**Secondary Outcomes** (data collected from KAP surveys and in-depth interviews):

1. Knowledge of contraceptive methods among HIV-positive clients
  - a. Will compare pre-intervention rates from baseline data to post-intervention data at intervention sites

- b. Will compare pre-intervention rates from baseline data to post-intervention data at control sites
  - c. Will compare post-intervention data from intervention sites to data collected over same time period from control sites
- 2. Knowledge of contraceptive methods among providers, including peer counselors, at HIV care and treatment centers
  - a. Will compare pre-intervention rates from baseline data to post-intervention data at intervention sites
  - b. Will compare pre-intervention rates from baseline data to post-intervention data at control sites
  - c. Will compare post-intervention data from intervention sites to data collected over same time period from control sites
- 3. Acceptability of family planning services
  - a. Will compare pre-intervention rates from baseline data to post-intervention data at intervention sites
  - b. Will compare pre-intervention rates from baseline data to post-intervention data at control sites
  - c. Will compare post-intervention data from intervention sites to data collected over same time period from control sites
- 4. Feasibility of providing family planning services at HIV care and treatment centers (data from post-intervention surveys of clinic staff)
- 5. Reproductive intentions of HIV-infected clients receiving care and treatment (data from baseline client surveys and in-depth interviews)

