  - a. The primary outcome upon which we based our sample size calculation is contraceptive prevalence. According to the 2003 Kenya Demographic and Health Survey, approximately 22% of women in a union in Nyanza Province use a modern contraceptive method. This level of contraceptive prevalence is similar to that seen among clients at the FACES sites. We would like to be able to detect a 8% rise in contraceptive prevalence to 30%.
- 3. Assumptions
  - a. Two-sided alpha of 0.05
  - b. Power of 0.8
  - c. Intra-cluster Correlation Coefficient of 0.01
- 4. Sample size.
  - a. Using these estimates, the needed sample size is approximately 140 women at each of the 18 sites, for a total sample of 2,520 women.
  - b. We plan to initially recruit a similar number, 2,520, of male clients, however our primary outcome for men will be the proportion of male clients who report they or their partner are interested in starting a new FP method after receiving FP counseling during their visit. In order to accurately calculate this sample size, baseline data is needed to estimate the baseline proportion of male clients who would express interest in starting a new FP method. Thus, after the baseline data collection phase a more accurate sample size for male clients will be calculated.

**KAP surveys.** Because the largest sample sizes are required for expected proportions nearer to 0.5 than to 0 or 1, we will take the worst-case scenario and assume that for each individual question on the survey approximately half of the participants will answer correctly. We hypothesize that people in the intervention sites will be more knowledgeable after the intervention at the end of the study, so we would like to test for at least a ten percentage point difference in correct answers among patients in the intervention sites (~60% correct) compared to patients in the comparison sites (~50% correct), as well as a 10% increase in correct answers among patients in the intervention sites compared to the baseline results. For a one-sided test of two proportions using two samples, power of 0.8, and an alpha level of 0.05, the required sample size is 325 patients from the intervention sites and 163 patients from the comparison sites for both men (N=488) and women (N=488).

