### **Informed Consent:**

#### **Baseline and follow-up surveys with male and female clients**

Male and female clients will be invited to participate in the surveys (both baseline and follow-up) after they have completed their visit at the PSC site. They will be given information about the study and their rights as a part of the informed consent process. If they agree to participate, they will be asked to sign an informed consent form. As part of this informed consent process, potential participants will be informed of: (1) the purpose and methods of the study, (2) procedures to protect the confidentiality, (3) their rights to withdraw from the study at any time, (4) the fact that their participation or non-participation will not affect the medical care that they receive, and (5) persons to contact if they have any questions about the study after the completion of the interview. The participating clients will also be given a copy of the consent form to keep. This page will include names and phone numbers of persons to contact with any questions regarding the study. The consent form for clients participating in the surveys is included in Appendix C. The interviewer will also ask follow-up questions to ensure that the informed consent process has been well understood by the potential participant.

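### The end-of-study client KAP survey takes a convenience sample after allocation at sites whose arm is visible, so respondent choice can bias the between-arm comparison of client knowledge and acceptability

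*Protocol*

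**What the plan says.** Section 3.2 (end-of-study client KAP survey) states that "a convenience sample of approximately 28 female clients and 28 male clients will be recruited from each of 18 sites". Section 1.2 uses the same method at baseline: "a convenience sample of approximately 28 female patients and 28 male patients will be recruited from each of the 18 sites". Under Informed Consent, clients in both rounds are invited "after they have completed their visit at the PSC site".

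Study and data management makes the interviewers/research assistants "responsible for abstraction of data from patient records and for conducting all interviews with clients and providers". No section gives a rule for choosing respondents or describes masking of interviewers.

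At intervention sites, section 2.2 says clients "will then be extensively counseled about contraception and will be provided any needed contraceptive methods on site"; control sites keep their standard mechanisms, generally referral. On timing, the Overview says: "After collecting the baseline data, we plan to stratify the clinics into two categories", with randomisation to follow.

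The secondary outcomes under Endpoints include client knowledge and acceptability. Each is compared with baseline within each arm and also between arms: "Will compare post-intervention data from intervention sites to data collected over same time period from control sites".

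**The concern.** A convenience sample leaves the choice of respondent to whoever does the approaching. In the end-of-study round that choice is made in an open trial. Clients are met as they finish a visit, so it may be apparent who has just had a family planning discussion. If such clients are more likely to be approached at intervention sites, the two arms' samples differ for a reason other than the effect of integration on the clinic population. Analysis cannot repair this afterwards, because the selection probabilities are unknown.

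The protocol's Limitations section accepts that sites may recruit with unequal enthusiasm and relies on randomisation to spread staff motivation evenly. Randomisation balances what sites were like before allocation. It does not balance how respondents are picked once services differ by arm. The Limitations section does not mention the convenience sampling.

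The stake is more than descriptive. Expected Application of Results makes roll-out depend partly on whether integration appears acceptable, and client acceptability is measured in this survey and in the open-ended interviews.

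**Working it through.** **Which round can be affected.** According to the Overview, baseline KAP data are collected in the first three months and sites are randomised afterwards. Arm-related selection is therefore possible only in the end-of-study round. Baseline matters for a different reason: if the two rounds pick different kinds of client, the within-arm change mixes real change with a change in sample.

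**The plan's own figure.** Sample size considerations gives 325 intervention and 163 comparison respondents per sex for 60% against 50% correct: "For a one-sided test of two proportions using two samples, power of 0.8, and an alpha level of 0.05". At 2:1 without continuity correction, the comparison arm needs

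(0.25 + 0.24/2) × (1.645 + 0.842)² / 0.10² ≈ 229,

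and the intervention arm 458. The stated figures do not reproduce; 325 is the per-arm number for 1:1 allocation with continuity correction. That is a separate matter. The planned 325 and 163 are used below as they stand.

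**What a selection shift would do (the shift is assumed).** With no true effect and 50% correct in both arms:

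- SE = √[0.25 × (1/163 + 1/325)] = 0.048, that is 4.8 points.
- One-sided error under a shift b = 1 − Φ(1.645 − b/SE).
- The two-sided version uses 1.96 and adds the far tail.

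| Assumed shift b | One-sided 5% becomes | Two-sided 5% becomes |
|---|---|---|
| 2 points | 11% | 7% |
| 3 points | 15% | 10% |
| 5 points | 27% | 18% |

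The two-sided column is shown because the Data analysis plan specifies two-sided tests.

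These figures ignore clustering. With about 27 respondents per site and the ICC of 0.01 that the protocol assumes for contraceptive prevalence, the design effect is 1 + 26 × 0.01 = 1.26 and the SE becomes 0.048 × √1.26 = 0.054. A 3-point shift then gives 1 − Φ(1.645 − 0.03/0.054) ≈ 14% one-sided.

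**How a shift of that order could arise (both inputs assumed).** Shift = excess share of counselled clients in the sample × their advantage in correct answers. For example, 0.20 × 0.15 = 3 points and 0.30 × 0.20 = 6 points. The excess share cannot exceed the share of leaving clients who were not counselled. If 90% were counselled, the excess is at most 0.10 and the shift at most 1.5 to 2 points for the same score differences.

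**The case against.** Several points against the concern are sound and limit it.

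- **Baseline.** A reader might infer that both rounds are selected with the arm known. The Overview does not support that, because no arm exists at baseline. The timeline table overlaps baseline work with training and implementation in February–March 2009, but it does not place randomisation before baseline.
- **Who chooses.** A reader might infer that clinic staff hand-pick respondents. The protocol does not say so: it assigns the interviews to study staff and is silent on selection. Its remark about uneven recruitment is not specific to this survey. That the arm is known is itself an inference from visible services and the absence of described masking.
- **The mechanism has a ceiling.** Family planning assessment is meant to enter every visit. If delivery is close to plan, most clients leaving an intervention site have just been counselled and there is little room to over-select them.
- **The remedy is partial.** Exit sampling over-represents frequent attenders and does not remove refusal bias.
- **Workload is real.** Each round has 976 interviews of 30–45 minutes, or 488 to 732 interview hours, and the budget has three interviewers. Some sites are small: the five Rongo sites average 1,338/5 ≈ 268 clients. If 65% are adult women, at most about 94 are men or children, so 28 men would be about 30% or more of those.

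The core of the point stands. None of these objections gives a reason to leave the choice open when the comparison is between visibly different arms. A next-eligible-client rule deals with the small sites.

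**Conclusion.** The end-of-study client KAP survey carries an avoidable risk of arm-related selection, and randomisation of sites does not remove it. It bears on the secondary between-arm comparisons of client knowledge and acceptability. Both primary outcomes come from encounter forms, so a reader should not extend the point to contraceptive prevalence or pregnancy.

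Size and direction are unknown. The 3-point example (5% rising to about 15% one-sided at 325 and 163, ignoring clustering) shows how sensitive the test is to a modest shift. It is not an estimate of the bias in this trial, and the documents do not support one. The conclusion rests on three features of the text: selection without a rule, recruitment after allocation, and services that openly differ with no masking described. The change is worth making because it is cheap and must be made before data collection.

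**What to change.** In sections 1.2 and 3.2, replace the convenience sample by one fixed rule, identical in both arms and both rounds:

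- Approach every k-th eligible client leaving the clinic, with k set from expected attendance that day.
- At low-volume sites, approach the next eligible client to leave once the interviewer is free.
- Keep a tally of clients approached and refusing.
- Continue until about 28 women and 28 men per site are interviewed.

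The number of interviews, the reimbursement per interview and the interviewers stay the same, and clients are already approached after their visit. Section 3.1 already uses a random sample of charts at each site, so selection by rule is not foreign to the study. The cost is a tally sheet, a short instruction to interviewers and possibly longer waits at small sites. The rule removes interviewer discretion only. Refusal bias remains, though the tally makes it visible, and so does the over-representation of frequent attenders. Both should be stated as limitations.

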### **3.3. End-of-study survey with clinic staff at sites**

In the final month of the study, 30-40 clinic providers will be contacted and will be administered a follow-up survey. We will attempt to interview the same providers who participated in the baseline interview, but due to staff turnover, this may not be possible. The questionnaire will cover the same topics as the baseline survey with additional questions examining the feasibility of offering family planning services in their site during the study period. The survey will include several open-ended questions that will be tape recorded (if the participant gives his/her consent), transcribed, translated to English (if interview not performed in English), and a content analysis will be performed using the qualitative software ATLAS.ti. Clinic staff will be reimbursed with a book voucher worth approximately USD\$5 (approximately 350 Kenyan Shillings at current exchange rate) for participating in the survey. The final version of the survey will be submitted to the IRB prior to initiating data collection.

In order to further assess the feasibility of integration of family planning into HIV care and treatment program, we also plan to collect data on the cost of setting up and providing integrated services compared to the referral-based services. Collection of the cost data will involve meetings, document review, and interviews with staff in each of the study clinics. Specifically, data collection will take place via (1) review of service registers in intervention and control settings, (2) review of locally- and centrally-stored financial records, (3) intervention and control clinic visits to confirm resource use and allocation findings, and (4) semi-structured interviews with key administrative, clinical and financial staff. Where possible, cost and output data collected at the facility level will be also be verified against centralized accounting systems. No identifiable patient-level data will be collected, and staff will not be reimbursed for participating in costing interview.

